## 1 INTRODUCTION

### 1.1 Preface

Outside of sub-Saharan Africa, *Plasmodium vivax* is becoming the predominant cause of malaria. Although prevention of relapses is crucial for reducing transmission of this important disease, only two drugs (primaquine and tafenoquine) are licensed for treatment of hypnozoites (the latent liver stages) of *P. vivax* and thus have potential to prevent relapses. Primaquine is the anti-relapse drug available in most endemic regions, but its widespread impact on health outcomes is limited by poor adherence to the standard 14-day course and concerns over the risk of drug-induced haemolysis in patients with glucose-6-phosphate dehydrogenase (G6PD) deficiency. Over the last few years, new tools and treatment strategies have been developed for better tolerated and more effective radical cure regimens. Short-course (7 days), high daily-dose primaquine has been shown to have similar efficacy compared with the same WHO-recommended total dose of 7mg/kg body weight administered over 14 days (Taylor W.J. et al. 2019) in areas with high risk of relapse. However, the higher daily dose in the 7 day regimen (1mg/kg) is associated with more adverse events, particularly an increased risk of haemolysis and gastrointestinal events. A semi-quantitative point-of-care G6PD test (SD Biosensor, ROK) has been developed and registered in Indonesia and the process of registration is underway in Papua New Guinea (PNG).

### 1.2 Purpose of the analyses

The aim of the SCOPE study is to determine the effectiveness and safety of introducing a revised case management package to facilitate well-tolerated and effective radical cure of patients with vivax malaria at 10 public health care facilities in Indonesia and Papua New Guinea.

The revised case management package has been prioritised and endorsed by the respective Ministries of Health and will include: 1) semi-quantitative point-of-care glucose-6-phosphate dehydrogenase (G6PD) activity assessment prior to treatment with primaquine, 2) prescription of high dose (7mg/kg body weight total) primaquine over 7 (**PQ7**), 14 (**PQ14**) days or 8 weeks (**PQ8W**), to all eligible patients presenting with *P. vivax* malaria, 3) patient education and counselling prior to treatment and supervision of the first dose of primaquine at the health care facility, 4) community-based clinical review at day 3 of primaquine treatment to encourage treatment adherence and facilitate detection and management of adverse events to treatment and 5) improved malariometric surveillance and pharmacovigilance.

## 2 Study Objectives and Endpoints

### 2.1 Study objectives

The overall objective of the SCOPE study is to determine the operational feasibility and cost-effectiveness of introducing the revised case management package for patients with vivax malaria to inform national antimalarial policy and practice.

This SAP is focused solely on the quantitative measures of operational feasibility, pharmacovigilance, safety and effectiveness in the Stage 1 and Stage 2 studies. A separate document will be prepared for the qualitative measures of operational feasibility and a health economics analysis plan (HEAP) will be prepared for the cost-effectiveness analyses.

#### 2.1.1. Stage 1 – Preliminary safety and feasibility study

**Primary objective:**

- S1.PO1 To determine the safety of PQ in patients prescribed different treatment regimens
- S1.PO2 Determine the risk of patients experiencing any AESI during treatment

**Secondary objectives:**

- S1.SO1 Determine the risk of patients experiencing severe GI AESI during treatment
- S1.SO2 Determine the risk of patients experiencing severe haemolysis AESI during treatment
- S1.SO3 Determine the risk of patients experiencing severe methaemoglobinaemia AESI during treatment
- S1.SO4 Determine the tolerability of PQ in patients prescribed different treatment regimens
- S1.SO5 Determine primaquine dosing accuracy by G6PD activity category
- S1.SO6 Determine the proportion of patients receiving a clinical review on day 3 and day 7 of PQ treatment

## 2.1.2. Stage 2 – Large-scale implementation and feasibility study

### Primary objective:

- S2.PO1 To determine the operational feasibility of implementing revised case management for patients with *P. vivax* malaria.

### Secondary objectives:

#### *Quantitative measures of operational feasibility*

- S2.SO1 Determine the proportion of health care practitioners who comply with the revised radical cure treatment algorithm
- S2.SO2 Determine the proportion of patients receiving a SD Biosensor G6PD test
- S2.SO3 Determine primaquine dosing accuracy by G6PD activity category
- S2.SO4 Determine the proportion of vivax malaria patients who are ineligible for daily primaquine and are incorrectly given primaquine (including infants, pregnant females and G6PD deficient patients)
- S2.SO5 Determine the proportion of vivax malaria patients that are reviewed on day 3
- S2.SO6 Determine the proportion of vivax malaria patients that adhere to their prescribed primaquine regimen

#### *Pharmacovigilance*

- S2.SO7 Determine the proportion of community-based health workers who correctly act on early signs of haemolytic anaemia and GI events
- S2.SO8 Determine the number of patients identified through the community surveillance system with serious adverse events

#### *Safety*

- S2.SO9 Determine the safety of PQ under real-world conditions
- S2.SO10 Determine the risk of patients experiencing at least one AESI during treatment
- S2.SO11 Determine the risk of patients experiencing severe haemolysis AESI during treatment
- S2.SO12 Determine the risk of patients experiencing severe GI AESI during treatment
- S2.SO13 Determine the risk of patients experiencing severe methaemoglobinaemia AESI during treatment
- S2.SO14 Determine the difference in severe anaemia prevalence between the pre- and post-implementation periods of the revised case management

### *Effectiveness*

- |         |                                                                                                                                                                                                                                                       |
|---------|-------------------------------------------------------------------------------------------------------------------------------------------------------------------------------------------------------------------------------------------------------|
| S2.SO15 | Determine if the incidence of symptomatic P. vivax malaria decreases after the introduction of the revised case management                                                                                                                     |
| S2.SO16 | Determine the difference in prevalence of P. vivax parasitaemia in patients presenting with fever between the pre- and post-implementation periods of the revised case management                                                              |
| S2.SO17 | Determine if the cumulative risk of representation to the same health facility with symptomatic P. vivax malaria within 6 months differs between the pre- and post-implementation periods of the revised case management                       |
| S2.SO18 | Determine if the cumulative risk of representation to the same health facility with symptomatic P. vivax malaria within 6 months differs between SCOPE and non-SCOPE patients in the post-implementation period of the revised case management |

## 2.2 Endpoints

### 2.2.1. Stage 1 – Preliminary safety and feasibility study

All endpoints refer to patients enrolled into Stage 1 treated with daily or weekly PQ.

#### **Primary endpoints:**

- |        |                                                                                                              |
|--------|--------------------------------------------------------------------------------------------------------------|
| S1.PE1 | Proportion of patients experiencing at least one SAE during treatment.                                       |
| S1.PE2 | Proportion of patients experiencing at least one AESI, SAE or other AE of at least grade 3 during treatment. |

#### **Secondary endpoints:**

- |        |                                                                                                                                                                                                                                                                                                             |
|--------|-------------------------------------------------------------------------------------------------------------------------------------------------------------------------------------------------------------------------------------------------------------------------------------------------------------|
| S1.SE1 | Proportion of patients with a gastrointestinal AESI during treatment.                                                                                                                                                                                                                                       |
| S1.SE2 | Proportion of patients with an AESI related to haemolysis during treatment.                                                                                                                                                                                                                                 |
| S1.SE3 | Proportion of patients with an AESI related to methaemoglobinaemia during treatment.                                                                                                                                                                                                                        |
| S1.SE4 | Proportion of patients permanently stopping PQ before the end of treatment. 

• Defined as the proportion of all patients enrolled who are given documented advice to permanently stop PQ during scheduled or ad hoc clinical review by a health professional

 |
| S1.SE5 | Proportion of patients receiving correct treatment based on G6PD activity.                                                                                                                                                                                                                                  |
| S1.SE6 | Proportion of patients who were reviewed on day 3 and day 7.                                                                                                                                                                                                                                                |

**Exploratory endpoints:**

|        |                                                                                                                                         |
|--------|-----------------------------------------------------------------------------------------------------------------------------------------|
| S1.EE1 | Maximum absolute fall in haemoglobin within the first 7 days                                                                            |
| S1.EE2 | Maximum proportional fall in haemoglobin within the first 7 days                                                                        |
| S1.EE3 | Reduction of >25% in haemoglobin to a concentration of < 7 g/dl                                                                         |
| S1.EE4 | POST HOC : Level of agreement between SD Biosensor and HemoCue for haemoglobin measurement at study clinics and in the community |
| S1.EE5 | POST HOC : Methaemoglobin concentrations on days 3 and 7                                                                         |

**2.2.2. Stage 2 – Large-scale implementation and feasibility study**

**Primary endpoint:**

|        |                                                                                                                                                                                                                                                                                                              |
|--------|--------------------------------------------------------------------------------------------------------------------------------------------------------------------------------------------------------------------------------------------------------------------------------------------------------------|
| S2.PE1 | Proportion of patients with P. vivax malaria who correctly receive all components of revised case management (including G6PD testing, correct treatment of PQ according to revised case management and G6PD activity, patient education, supervision of the first dose and community review on day 3) |
|--------|--------------------------------------------------------------------------------------------------------------------------------------------------------------------------------------------------------------------------------------------------------------------------------------------------------------|

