## 4 Sample size

### 4.1 Stage 1

In the Stage 1 preliminary study of the feasibility and safety of the implementation package, 4 health facilities will enrol 800 patients (~500 in Indonesia and ~300 in Papua New Guinea). Assuming 764 of these patients will have a G6PD activity >70% and be eligible for PQ7, and that the proportion of patients receiving short-course primaquine who have to stop therapy within 7 days is 5%, this sample size will produce a 95% confidence interval for the true proportion needing to stop treatment of +/- 1.55%.

### 4.2 Stage 2

**NOTE:** *Given slower than expected recruitment in Stage 1, the predicted patient recruitment in Stage 2 was revised down on 5 August 2024 to 70% of eligible patients (n=11,410) across Indonesia and Papua New Guinea. Additionally, an error was detected in the original power calculation for detection of a reduction in incidence of vivax malaria. In protocol vs 5.0, the total number of patients with vivax malaria recruited into the study was erroneously predicted to be 16,300 over 18 months (the initial timeframe for the study) when in reality this was the number of patients predicted over 12 months. This resulted in an underestimate of the monthly case incidence at each clinic and thus an underestimate of the power available for detection of an incidence reduction.*

*The revised and corrected power and precision calculations are provided below with the original erroneous calculations retained for reference. Power calculations for detection of an individual-level reduction in risk of vivax malaria recurrence are also provided.*

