### **S2.PE1 Proportion of patients with *P. vivax* malaria who correctly receive all components of revised case management**

Assuming 70% of patients enrolled into Stage 2 receive all components of the implementation package correctly, the revised Stage 2 sample size of **11,410** patients will give a 95% confidence interval for the true proportion of +/- 0.84%.

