### 5.2. Stage 2 – Large-scale implementation and feasibility study

The primary analysis objective for Stage 2 is to estimate the proportion of patients with *P. vivax* malaria who correctly receive all components of revised case management (including G6PD testing, correct treatment with primaquine according to revised case management and G6PD activity, patient education, supervision of the first dose and community review at day 3), as stated in section 2.2.2. The secondary analysis objectives for Stage 2 include estimating the proportion of patients with secondary safety, tolerability and clinical review endpoints. The effectiveness and safety of implementing revised case management for patients with *P. vivax* malaria will also be estimated using an interrupted time series design for the incidence of symptomatic *P. vivax* malaria episodes, survival analysis of the cumulative risk of representation with *P. vivax* malaria and before versus

after analyses of the prevalence of asexual *P. vivax* parasitaemia and severe anaemia in patients presenting to health facilities with fever.

All of the above estimates will be presented with 95% confidence intervals.

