### 6.2. Stage 2 – Large-scale implementation and feasibility study

The primary analysis of the endpoints in Stage 2 will include all patients enrolled across the 10 health facilities in Indonesia and Papua New Guinea from the start of the pre-implementation period to the end of the post-implementation period (estimated to be about 16,300 patients). Before versus after analyses of the prevalence of asexual *P. vivax* parasitaemia and severe anaemia from the cross-sectional surveys will be done on the full aggregated dataset of all patients enrolled in the surveys across the 10 study sites (aiming for 200 patients each health facility for each survey = 4,000 patients total).

Secondary analyses of patient-related study outcomes will be conducted for the following pre-specified subgroups:

- Patients from Indonesia & Papua New Guinea
- Patients from PNG, Indonesian Papua and Sumatra
- Study site
- Ethnic group
- Patients with G6PD activity >70%, ≥30% to ≤70% and <30%
- Patients prescribed PQ7, PQ14 and PQ8W
- Patients aged <5 years, 5-15 years and >15 years
- Males and females

All of the health facilities in the study are already collecting *P. vivax* malaria incidence data.

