## 8 Handling of Missing Values

We do not expect there to be any reason that calendar time month will be missing for any observations over the study period (pre-implementation, Stage 1 and Stage 2) at each of the 10 sites. This is based on our experience of routine data collection during the baseline data period (i.e. prior to pre-implementation stage). We will descriptively report the patterns of missingness for the outcome measures and other participant variables over time in each site. For all analyses, missing data will be handled using an available case analysis, i.e. missing data on any variable included in the analysis where the observation for an individual at that time point is missing is excluded from the analysis.

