### 9.2. Stage 2 – Large-scale implementation and feasibility study

For Stage 2, the proportion of eligible patients receiving all elements of the implementation package correctly, and other related outcomes, will be presented for all patients, as well as stratified by study country and health facility. Corresponding 95% confidence intervals of these outcomes will be calculated assuming a binomial distribution.

The change in the incidence of symptomatic *P. vivax* malaria episodes (S2.SE15 - effectiveness endpoint) between the pre-Implementation Stage and post-implementation stage (Stage 2) will be shown graphically using an interrupted time series graph. Following the recommendations of Turner et al. (2020) the following components will be displayed: the health facility site-level (aggregated) data points versus time point of measurement (e.g. monthly for primary outcome) as a scatter plot; the interruption time will be displayed with a vertical dashed line; and the pre-interruption and post-

interruption trend lines; and the counterfactual trend line (an example is given in Appendix 3, Figure 2).

The estimate of the effect of the implementation package will be determined by fitting a segmented regression model to the monthly health facility level data (Bernal J.L. et al. 2017). For the segmented regression model, we will estimate the impact of the revised case management as:

- a) a level change comparing six months post-implementation to pre-implementation stage (Figure 2).
- b) the difference in trends before and after introduction of the implementation package (i.e. slope change comparing post-implementation to pre-implementation stage) (Bernal J.L. et al. 2017) (Figure 2).

A binary indicator variable will take the value of 1 for all time points following the start of the stage 2 implementation package within each health facility site, and a value of 0 for all other timepoints. Health facilities also participating in stage 1 will have this data excluded from analysis as seen in Appendix 4: Figure 1. A sensitivity analysis will be performed where the binary indicator variable takes the value of 1 for all timepoints following the start of implementation, including both stage 1 and 2.

See Appendix 4: Figure 1 for the data to be included in the pre- and post-implementation periods for S2.SE15.

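### The Stage 2 primary endpoint S2.PE1 has inconsistent denominators, and the available-case rule removes patients with an unrecorded component instead of classifying them

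*SAP*

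**What the plan says.** The SAP describes the population of S2.PE1 in four ways.

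- **Patients with *P. vivax*.** The endpoint in 2.2.2 is the proportion of such patients with "malaria who correctly receive all components of revised case management". The analysis objective in 5.2 uses the same population.
- **Eligible patients.** The methods in 9.2 will present "the proportion of eligible patients receiving all elements of the implementation package correctly".
- **Patients enrolled into Stage 2.** The precision calculation in 4.2.1 reads "Assuming 70% of patients enrolled into Stage 2 receive all components of the implementation package correctly", with n = 11,410 and an interval of +/- 0.84%.
- **Enrolled patients over a longer window.** Section 6.2 states: "The primary analysis of the endpoints in Stage 2 will include all patients enrolled across the 10 health facilities". It then sets the window as "from the start of the pre-implementation period to the end of the post-implementation period (estimated to be about 16,300 patients".

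The note in 4.2 says that predicted recruitment was "revised down on 5 August 2024 to 70% of eligible patients (n=11,410". Section 4.2.1 gives 16,300 as the maximum number eligible, from 17,160 *P. vivax* patients less 5% ineligible.

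On missing data, Section 8 states: "For all analyses, missing data will be handled using an available case analysis". The affected observations are excluded. No exception is made for S2.PE1.

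**The concern.** S2.PE1 is the only primary endpoint of Stage 2 and carries the study's answer on operational feasibility. With recruitment planned at 70% of eligible patients, the enrolled and eligible populations differ by several thousand people. An analyst could report the proportion over either group, or over all *P. vivax* patients, and cite the SAP each time. Section 2.2.1 fixes the Stage 1 population in one opening sentence, but 2.2.2 has no counterpart.

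Section 6.2 does not settle the matter. Its window suits the before-and-after endpoints but not a measure of package delivery, because the pre-implementation period precedes the package.

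The missing-data rule raises a related question. S2.PE1 is a composite of five delivery steps: G6PD test, correct primaquine regimen, education, supervised first dose and day 3 review. For such an endpoint a blank field will often mean that the step did not happen. Section 8, followed literally, takes that patient out of both numerator and denominator.

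**Working it through.** **Inputs from the SAP.** 17,160 *P. vivax* patients a year at the ten clinics and 5% ineligible (4.2.1); 70% of eligible patients recruited (4.2); 70% of enrolled patients receive everything and a half-width of 0.84 points (4.2.1, S2.PE1).

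**The plan's own figures.** 17,160 × 0.95 = 16,302, rounded in the SAP to 16,300. 16,300 × 0.70 = 11,410. The binomial half-width is 1.96 × √(0.70 × 0.30 / 11,410) = 0.841 points. The stated 0.84 is therefore correct for the enrolled denominator.

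**Effect of the denominator.** Successes among enrolled patients are 0.70 × 11,410 = 7,987. Eligible patients not enrolled number 16,300 − 11,410 = 4,890. The SAP does not say how many of them would receive the full package, so let that share be q (assumption). The proportion among eligible patients is (7,987 + 4,890q) / 16,300.

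| q (assumed) | Calculation | Proportion of eligible |
|---|---|---|
| 0% | 7,987 / 16,300 | 49.0% |
| 20% | (7,987 + 978) / 16,300 | 55.0% |
| 50% | (7,987 + 2,445) / 16,300 | 64.0% |
| 70% | (7,987 + 3,423) / 16,300 | 70.0% |

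The two proportions agree only if non-enrolled patients do as well as enrolled ones. At q = 50% the gap is 6.0 points, about seven times the half-width (6.0 / 0.84 = 7.1).

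**The figure in 6.2.** About 16,300 matches the maximum eligible number, not the predicted enrolment of 11,410. It does not match the pre-plus-post total either: for S2.SE17, 4.2.1 counts 22,820 patients over both periods (2 × 11,410).

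**Effect of the available-case rule.** With S successes among N enrolled patients and M dropped for an unrecorded component, the rule reports S / (N − M). This is never below S / N, the value when those patients count as not received. Hold S / N at 70% and write m = M / N. The SAP gives no missingness rate, so m is assumed.

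| m (assumed) | Available-case estimate, 0.70 / (1 − m) |
|---|---|
| 2% | 71.4% |
| 5% | 73.7% |
| 10% | 77.8% |

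The estimate moves by the whole half-width when 0.70 / (1 − m) = 0.7084. That gives m = 1.2%, or about 135 of 11,410 patients.

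**The case against.** The strongest defence is that the SAP effectively settles on enrolled patients. Section 6.2 names them as the analysis set and 4.2.1 sizes the endpoint on them. The wording in 2.2.2 and 5.2 can be read as a label, and 3.2 makes signed agreement to participate an inclusion criterion, so eligible could mean enrolled. Part of this stands: enrolled is the likeliest intention. But 4.2 and 4.2.1 use eligible for the 16,300 of whom 70% are recruited, and the window and number in 6.2 conflict with 4.2.1.

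A reader might infer that the reported result will be too high by 21 points (70.0% against 49.0%), or by 23.5 points against all *P. vivax* patients (7,987 / 17,160 = 46.5%). The document does not support that. Both figures assume that no non-enrolled patient receives the full package, and the second also counts ineligible patients as delivery failures. Nor does every inconsistency inflate: including pre-implementation patients, as 6.2 literally does, would lower the proportion.

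A reader might also infer that all eligible patients is the only valid denominator. It is not. The proportion among enrolled patients measures fidelity; the proportion among all eligible patients measures reach, and mixes declining to take part with failure of delivery. Both are legitimate if named.

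On missing data, a step recorded as not done is not a missing value. The baseline form in Appendix 1 has a field for whether the first primaquine dose was observed, with a reason if not. Table S1a counts patients without a day 3 review over all enrolled. These steps are therefore partly covered. A blanket rule that unrecorded means not received would also misfire: the only education field listed in Appendix 1 is on the Level 2 review form, so patients without that review would nearly all fail. What remains is that Section 8 gives the composite no classification rule and, as written, excludes the patient.

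**Conclusion.** The inconsistency is real and lies wholly within the SAP. S2.PE1 is taken over *P. vivax*, eligible and enrolled patients in different sections, and the analysis set in 6.2 has an unsuitable window and an outdated count. If 70% of enrolled patients succeed, choosing eligible patients instead lowers the estimate by 6 to 21 points for q between 50% and 0%. The available-case rule raises it by 1.4 to 7.8 points, relative to counting unrecorded components as not received, for m between 2% and 10%. Both ranges rest on assumed shares. Whether the available-case value exceeds the truth depends on how often unrecorded means not done. The +/- 0.84% itself is correct for its denominator.

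This should be fixed before analysis. It is not graver than that, because S2.PE1 is a descriptive proportion with a binomial interval, and this document attaches no hypothesis test or success threshold to it.

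**What to change.** 1. In 2.2.2, 4.2.1, 5.2, 6.2 and 9.2, name one denominator for S2.PE1, restricted to the Stage 2 post-implementation period. Report two labelled proportions: among enrolled patients, and among all primaquine-eligible *P. vivax* patients presenting. State how receipt is established for non-enrolled patients.
2. In 6.2, give S2.PE1 its own window, separate from the before-and-after endpoints, and replace the figure of about 16,300 with 11,410.
3. In Section 8, exempt S2.PE1, S2.SE2, S2.SE3 and S2.SE5 from available-case exclusion. Name the source variable for each component. Where the field is collected for every patient (G6PD result, primaquine regimen, first dose observed, day 3 review), count an unrecorded component as not received, with available-case as a sensitivity analysis.
4. Name the data source for patient education before applying that rule to it.

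The cost is SAP wording, the work of mapping components to variables, one extra reported proportion, and possibly a lower headline figure.
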